#### Qualitative data collection

We will use SSIs after the trial follow-up to explore the views of participants and carers from both trial arms, physicians, traditional healers and decision-makers with responsibilities for developing or implementing health policy in the directorate of health for future implementation and evaluation. Around four to six separate interviews will be conducted with each group. The SSIs will explore the (1) acceptability of educational materials and delivery, (2) acceptability of evaluating THE HOPE in a definitive trial, (3) burden of training, (4) barriers and facilitators to early detection and collaboration with mental health services, and (5) overall satisfaction with the intervention. Participants for these interviews will be purposively sampled to stratify by gender and urban setting. An SSI topic guide will be used to facilitate the interviews.

##### Process evaluation

We will conduct (1) interviews with those receiving and delivering THE HOPE (assess acceptability) and (2) interviews with healthcare decision-makers (to support implementation) for the evaluation of training (pretraining and post-training scores).

### Withdrawal criteria

There are no anticipated risks involved for those who decide to take part in this study. The study includes sharing personal experiences, which some may find uncomfortable. Participants are under no obligation to answer any questions that make them feel uncomfortable. The information received from the participant will not be used in any way that might cause any harm. Participants will be informed that if there is any problem throughout the participation, the trained mental health professionals will be available for help.

Participants will be informed that they can withdraw from the study at any time without giving a reason and that their clinical care will not be affected. Participants will be withdrawn from the study in the event of any of the following: (1) non-compliance with the study protocol that results in a serious breach of protocol (Good Clinical Practice or other), which can compromise data integrity or significantly affect the scientific value of the reported results; (2) a serious untoward incident compromising the patient’s safety. Any data collected up to the point of discontinuation from the study will be reported as such.

Patients requiring inpatient admission or electroconvulsive therapy or any other therapeutic procedure as part of the treatment or exacerbation of the symptoms will not be discontinued from the study, provided that the procedure is as advised by their treating psychiatrist and the patient continues to consent for the study.

In case of reported harm to the participants directly because of receiving the treatment or the control, the harms will be reported to the Data and Safety Monitoring Board (DSMB) and Trial Steering Committee (TSC), who will further advise if the trial needs to be stopped.

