### Data analysis

#### Quantitative analysis

Being a feasibility trial, the main analysis will focus on process outcomes and include estimation (with one-sided and two-sided 80% and 90% CI estimation) of the number/proportion of potentially eligible patients, consent rate, overall uptake rate (in relation to number potentially eligible), average cluster sizes (and variation in cluster sizes) and treatment fidelity—the proportion of patients having the protocolled intervention pathway (intervention arm), intervention acceptability, assessment of possible contamination effect across clusters, overall retention/follow-up rate of participants. Our point and interval estimates will be considered alongside target success criteria for informing overall feasibility and potential progress to a main RCT.

We will also calculate means and CIs of clinical outcomes (both within-study and between-study groups) and determine which outcome(s) is/are most sensitive to change, and evaluate parameters required in order to inform the sample size calculation for the main trial.

Due to the lack of similar studies in this area, it is not possible to suggest clear progression criteria to guide the decisions about the feasibility of proceeding to a definitive trial in future. We suggest following a priori progression criteria in order to guide the feasibility of a future definitive trial. In light of the following criteria, the trial findings will be presented to the steering committee, which will advise about the feasibility of proceeding to the definitive trial.

**Red**, that is, the progression to a definitive trial using the proposed intervention and procedures is not feasible. Recruitment below 90 in total (45 in both arms) over a 12-month period, less than 70% of recruited sample completed all follow-up visits, and less than 70% of TSHs in both arms consented, participated in the training and worked with psychiatric services in referring the suspected cases.

**Amber**, that is, the progression to a definitive trial using the proposed intervention is feasible but would require modifications in the intervention, recruitment or follow-up procedures. Recruitment of 90–130 participants in total over a 12-month period, 70%–80% of recruited sample completed all follow-up visits, and 70%–85% of TSHs in both arms consented, participated in training and worked with psychiatric services in referring the suspected cases.

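### Two triggers take consenting participants out of the study itself, so their 12-week outcomes are lost and they count against the retention criterion

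*Protocol article*

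**What the plan says.** Under Withdrawal criteria, the protocol article first lets participants leave at any time without giving a reason. It then adds a rule that does not depend on their wishes: "Participants will be withdrawn from the study in the event of any of the following". Two triggers follow. The first is non-compliance resulting in a serious breach, of a kind that could damage data integrity or the scientific value of the results. The second is "a serious untoward incident compromising the patient’s safety". On data, the section says: "Any data collected up to the point of discontinuation from the study will be reported as such".

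The next paragraph is an exception. "Patients requiring inpatient admission or electroconvulsive therapy or any other therapeutic procedure" for treatment or for worsening symptoms "will not be discontinued from the study, provided that the procedure is as advised by their treating psychiatrist" and the patient continues to consent.

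Under Quantitative analysis, retention is one of three progression criteria. Red is "less than 70% of recruited sample completed all follow-up visits", Amber is "70%–80% of recruited sample completed all follow-up visits", and Green is above 80% of the same recruited sample. Table 1 schedules the Brief Psychiatric Rating Scale at 4 weeks and most other outcomes at baseline and 3 months. The Medication Adherence Rating Scale appears at 3 months only.

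**The concern.** The rule does not separate leaving the allocated care pathway from leaving follow-up. A patient who meets a trigger is removed from the study even if willing to attend the remaining visits.

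Two things follow. First, the missing 12-week values are unlikely to be missing at random, because serious non-compliance and serious safety incidents are plausibly linked to symptoms, adherence and engagement. The objectives use the means and standard deviations of these outcomes to size a definitive trial. Second, retention is meant to show whether patients can be followed up. A patient removed by rule remains in the denominator and cannot complete, so the figure partly measures the trial's own removal rule. A later analysis plan cannot repair either effect, because it cannot recover visits that were not made.

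There is also an overlap. A serious safety incident that leads to admission falls under both the second trigger and the exception, and the text does not say which prevails.

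**Working it through.** **The plan's own precision figure.** The Sample size section gives a margin of 0.1 for one arm and 0.07 overall for a 90% one-sided lower bound on a proportion such as retention. With margin = z(0.90) × √(p(1−p)/n) and p = 0.5:

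- n = 45: 1.2816 × √(0.25/45) = 0.0955, which rounds to 0.1.
- n = 90: 1.2816 × √(0.25/90) = 0.0675, which rounds to 0.07.

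The stated figures reproduce.

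**Inputs for retention.** The minimum sample is N = 90 (Sample size). The denominator is the recruited sample, and the cut-offs are 70% and 80% (Quantitative analysis). At N = 90 these are 0.70 × 90 = 63 and 0.80 × 90 = 72 completers. Exactly 72 is Amber, because Green needs more than 80%. Exactly 63 is Amber, because Red needs less than 70%.

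**Effect of the rule.** Let c be the number who would complete if follow-up were kept, and w the number removed by rule who would otherwise have completed. Retention is then (c − w)/90, a loss of 1/90 = 1.11 points per patient. The protocol article gives no expected w. The range below is an assumption, as is the premise that each removed patient would have completed.

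| w | Points lost | From 74/90 = 82.2% | From 68/90 = 75.6% | From 65/90 = 72.2% |
|---|---|---|---|---|
| 1 | 1.1 | 81.1% (Green) | 74.4% (Amber) | 71.1% (Amber) |
| 2 | 2.2 | 80.0% (Amber) | 73.3% (Amber) | 70.0% (Amber) |
| 3 | 3.3 | 78.9% (Amber) | 72.2% (Amber) | 68.9% (Red range) |
| 5 | 5.6 | 76.7% (Amber) | 70.0% (Amber) | 66.7% (Red range) |

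Near a cut-off, two or three patients change the retention band. From mid-Amber, five do not. With 131 recruits each removal costs 1/131 = 0.76 points, and 107/131 = 81.7% falls to 104/131 = 79.4% with three. Five removals at N = 90 cost 5.6 points, a little under the 6.75-point margin above. Unlike sampling error, this loss always acts downward.

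**Effect on outcomes, read against Table 1 and the Secondary outcome measures section.**

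- Adherence has no assessment before 3 months, so a patient removed earlier contributes no value.
- Remission must be maintained for 3 months and cannot be established for a patient removed earlier.
- Disengagement includes refusing treatment or 4 consecutive weeks without response. Removal cuts the period in which it can be observed.

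**The case against.** The strongest case on the other side is that this is a rare event in a 12-week feasibility trial with no formal hypothesis testing, and that a journal article may leave handling after withdrawal to the full protocol or its operating procedures. Several stronger readings that a reader might draw are indeed not supported:

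- **That ordinary poor engagement leads to removal.** The first trigger needs a serious breach. Refusal of treatment and non-response are measured outcomes (disengagement), and nothing says such patients are withdrawn.
- **That worsening patients in general are removed, so the 12-week results describe a better-faring group.** The exception for admission, electroconvulsive therapy and other procedures keeps many of them in. Selective loss is plausible for the few who meet a trigger, but its effect on the means is not shown.
- **That follow-up for harms stops.** The Safety and adverse events reporting section sets reporting duties and does not say they end at withdrawal.
- **That the rule would flip the progression decision.** Red joins its three conditions with 'and', so low retention alone does not literally give Red. The criteria are offered as a guide, interval estimates are considered alongside, and the steering committee advises.

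It is also true that the end of data collection is inferred: the text says that data up to discontinuation are reported, not that later data are refused. And a patient who has had a serious breach or incident might not have completed anyway, so w above is an upper figure for a given number of removals.

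What remains is that the article does not merely omit detail. It states a mandatory withdrawal from the study, with no condition on consent, next to a retention criterion that counts such patients as failures. The overlap with the exception also stands.

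**Conclusion.** The point holds as a limited defect in a stated rule. Participants meeting either trigger leave the study even if they still consent, and no later assessment is described. They would lack 12-week outcomes for reasons plausibly related to outcome, and each would lower retention by about 1.1 points at N = 90. Few patients are likely to be affected and the number is unknown. The consequence for the retention band is material mainly when retention lies within a few patients of 63 or 72 completers out of 90. This rests on two assumptions: that withdrawal from the study ends assessments, as the wording implies, and that some of those removed would have attended. The overlap between the second trigger and the exception is a separate inconsistency in the text and needs no assumption. The change is worth making before recruitment because it is cheap and the lost visits cannot be recovered later.

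**What to change.** In Withdrawal criteria, separate leaving the allocated pathway from leaving follow-up. State that meeting trigger (1) or (2) does not end the scheduled 4- and 12-week assessments or safety follow-up unless the participant withdraws consent to data collection. Reconcile the second trigger with the paragraph on admission and other procedures, so that it is clear how a patient covered by both is handled.

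Keep the retention definition and its recruited-sample denominator, and report any investigator-initiated withdrawals separately beside it. Removing such patients from the denominator is not advised because it can flatter the figure: with 74 potential completers and two removals, 72/90 = 80.0% would become 72/88 = 81.8%.

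The cost is a wording change, with any approval it needs, and a few assessments that are already scheduled. The change concerns data collection only and takes no position on treatment.

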### Study timeline

We aim for the pilot RCT to start on 1 April 2023. Recruitment will commence when the trial commences and will be conducted until 1 April 2024; there will be a 3-month follow-up after the recruitment of the last patient. We anticipate that the analysis will start in September 2024.

### End of trial

The end of the study is defined as when the 12-week follow-up assessment and all qualitative interviews have been completed. Keele University ethics and the ethics board in the local context will be notified of the end of the study.

### Data management

All data will be managed in line with the protocol and will be stored securely following the KMU and Keele University standard policy on data storage and confidentiality. Individual participant data will be pseudonymised through the use of a unique study ID and will be stored securely and separately from any identifiable data. Access to data will be restricted to members of the Keele and KMU research team and will be stored in accordance with standard operating procedures. Outcome data will be entered into an electronic database which will be stored on an encrypted secure network at KMU, requiring a password to access. Data entry will be quality-checked and coded using standard processes.

### Data analysis

#### Quantitative analysis

Being a feasibility trial, the main analysis will focus on process outcomes and include estimation (with one-sided and two-sided 80% and 90% CI estimation) of the number/proportion of potentially eligible patients, consent rate, overall uptake rate (in relation to number potentially eligible), average cluster sizes (and variation in cluster sizes) and treatment fidelity—the proportion of patients having the protocolled intervention pathway (intervention arm), intervention acceptability, assessment of possible contamination effect across clusters, overall retention/follow-up rate of participants. Our point and interval estimates will be considered alongside target success criteria for informing overall feasibility and potential progress to a main RCT.

We will also calculate means and CIs of clinical outcomes (both within-study and between-study groups) and determine which outcome(s) is/are most sensitive to change, and evaluate parameters required in order to inform the sample size calculation for the main trial.

Due to the lack of similar studies in this area, it is not possible to suggest clear progression criteria to guide the decisions about the feasibility of proceeding to a definitive trial in future. We suggest following a priori progression criteria in order to guide the feasibility of a future definitive trial. In light of the following criteria, the trial findings will be presented to the steering committee, which will advise about the feasibility of proceeding to the definitive trial.

**Red**, that is, the progression to a definitive trial using the proposed intervention and procedures is not feasible. Recruitment below 90 in total (45 in both arms) over a 12-month period, less than 70% of recruited sample completed all follow-up visits, and less than 70% of TSHs in both arms consented, participated in the training and worked with psychiatric services in referring the suspected cases.

**Amber**, that is, the progression to a definitive trial using the proposed intervention is feasible but would require modifications in the intervention, recruitment or follow-up procedures. Recruitment of 90–130 participants in total over a 12-month period, 70%–80% of recruited sample completed all follow-up visits, and 70%–85% of TSHs in both arms consented, participated in training and worked with psychiatric services in referring the suspected cases.

**Green**, that is, the progression to a definitive trial using the proposed intervention is feasible without changes in the intervention, recruitment or follow-up procedures.

Recruitment of more than 130 participants in total over a 12-month period (averaging at least about 1.5 patients recruited per UC), more than 80% of the recruited sample completed all follow-up visits and >85% proportion of TSHs in both arms consented, participated in training and worked with psychiatric services in referring the suspected cases.

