### Sample size

This being a feasibility study, we do not provide a power calculation as there is no proposal for formal hypothesis testing, and the sample size focuses on the required precision of feasibility parameters in line with recommendations for pilot and feasibility studies.^21^ FEP has a relatively low incidence of about 26.6 per 100 000 person-years.^22^ In order to obtain an adequate sample size to measure feasibility outcomes, we will include all UCs in district Peshawar (n=93) in the sample, allocated to ETAU and THE HOPE arm in a 1:1 ratio. We will aim to recruit a minimum of 90 patients (45 in each arm) over a 12-month period. We believe this will help us to achieve reasonable precision of feasibility estimates, for example, for evaluation of intervention fidelity and participant retention in the study (as a proportion). This will enable the 90% one-sided lower confidence bound to be derived to a margin of error of 0.1 for single-arm evaluation and 0.07 for overall sample evaluation. This fits the criteria for sample size justification and calculation recommendations for pilot and feasibility studies.^23^

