### Identification of the PCPs and TSHs

We will select 20 TSHs who will be linked with five PCPs working in the local primary healthcare centres in each arm of the study. A group of five TSHs will be linked with one PCP working in the nearest primary healthcare centre. The PCPs will be randomly selected in both intervention and control arms and will be linked to TSHs. The selection will be made by the Department of Family Medicine at KMU.

Our previous work in this area has identified three types of TSH: (1) Pirs (spiritual leaders in Sufi tradition) with well-established shrines, (2) imams, spiritual leaders based in mosques and (3) traditional healers who practise traditional methods such as (taweez) alms or herbs. After consultations with community elders, 20 TSHs in each arm will be selected based on (1) an established reputation for treating mental health problems and not using harmful practices, and (2) willingness to work with the healthcare system.

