### Recruitment

Participants suspected of having FEP will be identified from the following possible sources: (1) potentially eligible participants seen by TSHs, (2) potentially eligible participants identified by the PCPs, (3) those presenting in mental health services with suspected FEP and have been in contact and receiving treatment from a TSH in the area.

The cluster allocation will determine the treatment path for each participant. It is possible, for example, that a potentially eligible patient residing in the control cluster presents to the TSH in the intervention arm and vice versa. In such a case, the patient will be given the choice of visiting the nearest TSH based in the control arm (and vice versa). Otherwise, he/she will not be included in the study.

To avoid any selection bias in both groups, the recruitment into the study (both arms) would be done using the same methods by an independent researcher who would enrol in a non-selection bias way that gives parity/equality in uptake. The baseline information about all suspected cases of psychosis by TSHs will be collected, including symptomatology and demographic features. Those with a confirmed diagnosis of psychosis (by the psychiatric team following the procedures given below) will be treated in one of the treatment arms.

Potential participants will be verbally informed about the trial by the TSHs, PCPs or research assistant (RA) working with the research team. Patients who agree to participate will be given a full written information sheet about the study by an RA (written information sheets read by RA for those who cannot read) about the study. In case of a young person below the age of 16 years, written informed consent will be obtained from the patient and the parent, who will almost always be accompanying the young person (online supplemental appendices 1 and 2). For illiterate participants, witnessed oral consent and a thumbprint in lieu of a signature will be sufficient. The witness will not be a member of the research team. Both alternatives to full written consent are routinely practised in Pakistan, are culturally acceptable and have been used in our previous studies in this setting^27 29^ (see figure 2).

10.1136/bmjopen-2023-072471.supp1Supplementary data

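### The healer stop–go percentage mixes willingness to collaborate with how many suspected cases the healers happen to meet

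*Protocol article*

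**What the plan says.** The criteria are in the protocol article under Data analysis, Quantitative analysis. The healer item is the third condition in each band:

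- Red: "less than 70% of TSHs in both arms consented, participated in the training and worked with psychiatric services in referring the suspected cases".
- Amber: "70%–85% of TSHs in both arms consented, participated in training and worked with psychiatric services in referring the suspected cases".
- Green: ">85% proportion of TSHs in both arms consented, participated in training and worked with psychiatric services in referring the suspected cases".

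Under Identification of the PCPs and TSHs, "20 TSHs in each arm will be selected", which makes 40 in all. The Sample size section states: "We will aim to recruit a minimum of 90 patients (45 in each arm) over a 12-month period". The Green band asks for "Recruitment of more than 130 participants in total over a 12-month period".

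The Recruitment section names three sources of patients: TSHs, primary care physicians (PCPs), and "those presenting in mental health services with suspected FEP" who have also been under the care of a healer in the area. That healer is not said to be one of the 40.

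The article does not limit the referral element to TSHs who met a suspected case, and it does not say how to class a TSH who met none. Among the secondary outcomes, willingness of TSHs is measured by the numbers approached, consenting and completing training, with no referral element.

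**The concern.** The item asks whether healers will take part and work with psychiatric services. To count, a TSH must satisfy three things at once. Two are in the TSH's hands: consent and training. The third also needs a suspected case to turn up within the recruitment period. The Sample size section itself describes first-episode psychosis as having a low incidence, and two of the three recruitment routes do not start with a trial healer.

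A fully cooperative healer network could therefore score Red or Amber because too few cases reached some of its members. A steering committee reading that colour as poor collaboration would be misled about the acceptability of the intervention, on one of only three pre-set progression items.

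**Working it through.** **Plan's own figure.** The article gives no expected value for the healer percentage. The nearest calculated figure is the precision statement in Sample size. At p = 0.5, 1.2816 × √(0.25/45) = 0.0955 and 1.2816 × √(0.25/90) = 0.0675, which round to the stated 0.1 and 0.07. It concerns patient proportions and is not affected by this point.

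**Inputs from the article.** 40 TSHs; cut-offs of 70% and 85%; 90 recruits as the minimum and more than 130 for Green.

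**Inputs assumed, because the article gives none.** The share of recruits who come through TSHs, the number of suspected cases per recruit, and how evenly cases are spread over TSHs.

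**Bands in whole healers.** 70% of 40 is 28 and 85% is 34. Red is 27 or fewer, Amber 28 to 34, Green 35 or more. Thirteen TSHs without a case are enough for Red.

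**Best case for collaboration.** All 40 consent, train and refer every case they suspect. If N suspected cases fall at random on 40 TSHs, the expected share with at least one is 1 − (1 − 1/40)^N, close to 1 − exp(−N/40).

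**Break-even, equal caseloads.** N = −40 × ln(0.30) = 48.2 for 70%, and N = −40 × ln(0.15) = 75.9 for 85%. That is about 1.20 and 1.90 cases per TSH.

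**Break-even, uneven caseloads.** With gamma-varying caseloads of shape k and mean m per TSH, the share is about 1 − (1 + m/k)^(−k).

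- k = 2: 70% needs m = 2 × (0.30^(−1/2) − 1) = 1.65, about 66 cases. 85% needs m = 2 × (0.15^(−1/2) − 1) = 3.16, about 127 cases.
- k = 1: 70% needs m = 1/0.30 − 1 = 2.33, about 93 cases. 85% needs m = 1/0.15 − 1 = 5.67, about 227 cases.

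**Scenarios.** Each cell gives the expected share and the probability that the item is Red, from 20,000 simulated allocations of N cases to 40 TSHs.

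| Scenario | N | Equal | k = 2 | k = 1 |
|---|---|---|---|---|
| 90 recruits, all via TSHs, 1 suspected per recruit | 90 | 90%; about 0 | 78%; 0.04 | 70%; 0.43 |
| 90, half via TSHs, 2 per recruit | 90 | 90%; about 0 | 78%; 0.04 | 70%; 0.43 |
| 90, one third via TSHs, 2 per recruit | 60 | 78%; 0.03 | 68%; 0.56 | 61%; 0.92 |
| 90, half via TSHs, 1 per recruit | 45 | 68%; 0.55 | 60%; 0.95 | 54%; 0.997 |
| 130, one third via TSHs, 1 per recruit | 43 | 66%; 0.69 | 58%; 0.97 | 53%; 0.998 |
| 90, one third via TSHs, 1 per recruit | 30 | 53%; about 1 | 48%; about 1 | 44%; about 1 |

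**Sensitivity to the suspected-to-recruited ratio.** At 90 recruits with half via TSHs and equal caseloads, the expected share leaves Red at 48/45 = 1.07 suspected cases per recruit and reaches 85% at 76/45 = 1.69. With one third via TSHs the figures are 48/30 = 1.6 and 76/30 = 2.5.

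Collaboration is perfect in every row, so the spread in colour comes only from case volume and its distribution.

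**The case against.** The strongest reply has four parts.

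1. **The no-case rule is not express text.** A reader might infer that the protocol scores a TSH with no case as a failure. It does not say so. A TSH who joined the pathway and held back nobody could be called compliant. The denominator of 40 is also inferred, since counting consent in the numerator suggests that healers approached might be meant. This stands as a limit on the wording. It does not rescue the criterion, because the same data can then give different colours under two readings of a pre-set threshold. Under full cooperation everyone approached consents, so the two denominators coincide.

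2. **Red is not the expected result.** A reader might infer from the 68% figure that Red is likely at the minimum recruitment. That figure needs nearly every TSH-suspected case to be confirmed, eligible and consenting. The article treats confirmation as an outcome and does not assume it. TSHs are also selected partly for a reputation in treating mental health problems, which favours higher caseloads. This stands in full: the documents support only a range that runs from Red to Green.

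3. **The item does not decide the verdict.** A reader might infer that a Red healer percentage stops progression. The three Red conditions are joined by *and*, recruitment of 90 or more is not Red, and the steering committee advises with other healer data before it. This also stands.

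4. **Few active healers is itself a feasibility signal, and a naive split would be empty.** Under Study procedures the research assistant refers all suspected cases, and the TSH's judgement is recorded on an instrument in that same process. A referral percentage limited to TSHs with a recorded case would be close to 100% by construction. This is right, and the fix has to allow for it.

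A reader might also infer that a productive PCP or hospital route must lower the item. That holds only if total recruitment is fixed, and 90 is a minimum.

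**Conclusion.** The concern holds in a limited form. On its literal reading, the healer item combines willingness with case volume, and its colour can be wrong as a measure of collaboration. With 40 fully cooperative TSHs, about 48 TSH-seen suspected cases are needed before the expected share reaches 70%, and about 76 before it reaches 85%, if caseloads are equal; uneven caseloads raise both. Whether those counts are reached depends on three quantities that the article does not give.

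The consequence is a misleading colour on one item, not an automatic stop. As the Green conditions are also joined by *and*, the item could keep a trial out of Green. With 131 recruits, half via TSHs and one suspected case each (about 65 cases), the expected share is about 81%, which is Amber despite full cooperation.

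This should be changed before the criteria are applied. The protocol itself fixes the thresholds, so it is not a detail that the analysis plan would be expected to supply.

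**What to change.** Split the healer item in all three bands.

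- **(a) Participation.** Consented and completed training, as a percentage of all selected TSHs, keeping the 70% and 85% cut-offs.
- **(b) Referral.** TSHs who worked with services in referral, as a percentage of those with an opportunity to refer. Opportunity means that the TSH recorded a suspected case, or is identified as having treated a patient who reached the study through a PCP or mental health services. Missed referrals then count against the item, so it is not self-fulfilling.
- **Beside (b).** The number and percentage of all TSHs with no suspected case, so that the committee still sees non-detection.

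The cost is a few sentences in the progression criteria. Training counts, suspected cases and the TSH instrument are already planned. The one addition is to record which healer was seen by patients arriving through the other two routes. The downside is that (b) rests on fewer than 40 healers and is less precise.

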### Study setting

The study will be carried out in Peshawar district, the capital city of KP province in Pakistan. District Peshawar has a population of about 4 million. The district has 93 union councils (UCs) as basic administrative divisions. Each UC has, on average, a population of about 20 000 and is served by a primary healthcare centre called Basic Health Unit (BHU), providing essential primary healthcare services. The mental health services are provided mainly in three teaching hospitals in Peshawar with about 20 qualified psychiatrists.

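### The per-UC average in the Green recruitment criterion does not match its total: more than 130 over 93 UCs is about 1.4 per UC, not 1.5

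*Protocol article*

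**What the plan says.** The progression criteria in the Protocol article (Data analysis, Quantitative analysis) set three recruitment bands as totals, the last with an added gloss in parentheses:

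- Red: "Recruitment below 90 in total (45 in both arms) over a 12-month period"
- Amber: "Recruitment of 90–130 participants in total over a 12-month period"
- Green: "Recruitment of more than 130 participants in total over a 12-month period (averaging at least about 1.5 patients recruited per UC"

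The per-UC average appears only in the Green band. The number of UCs comes from Sample size: "we will include all UCs in district Peshawar (n=93) in the sample". The same section heading (Quantitative analysis) lists average cluster size, and its variation, among the quantities to be estimated.

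On a separate matter, Study setting describes the catchment twice. It says "District Peshawar has a population of about 4 million", gives 93 UCs as the district's basic divisions, and says "Each UC has, on average, a population of about 20 000".

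**The concern.** A gloss on a threshold should restate it in other units. Here the total and the per-UC average differ by nine participants at the margin, and the gloss is phrased as a lower limit. Because mean cluster size is a planned estimate, the steering committee will probably see the mean beside the total. For some results the total would say Green while the mean would lie below the figure printed in the Green criterion. Green and Amber carry different advice: proceed unchanged, or proceed after modifying the intervention, recruitment or follow-up. The text should leave no room to argue between them once results are known.

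The two descriptions of the catchment population also disagree, by more than rounding can explain.

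**Working it through.** **Inputs.** Green total: more than 130, so 131 at the least (Quantitative analysis). Per-UC gloss: 1.5 (same place). Clusters: 93 (Sample size; also Study setting). Amber upper limit: 130 (Quantitative analysis).

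**Step 1, try to reproduce the plan's figure.** Average per UC = total / number of UCs.

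- 130/93 = 1.398
- 131/93 = 1.409

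Neither gives 1.5. The gloss exceeds the value at 131 by (1.5 − 1.409)/1.5 = 6.1% of the stated figure.

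**Step 2, work back from 1.5.** Total = 1.5 × 93 = 139.5, so 140 is the first whole number that meets it. Relative to 131 this is (139.5 − 131)/131 = 6.5% higher.

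**Step 3, see whether rounding explains it.** The lowest total whose mean rounds to 1.5 at one decimal is the first whole number at or above 1.45 × 93 = 134.85, which is 135.

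| Total | Mean per UC (93 UCs) | Band by total | Mean to one decimal |
|---|---|---|---|
| 130 | 1.398 | Amber | 1.4 |
| 131 | 1.409 | Green | 1.4 |
| 135 | 1.452 | Green | 1.5 |
| 139 | 1.495 | Green | 1.5 |
| 140 | 1.505 | Green | 1.5 |

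Totals of 131 to 139 are Green but fall below 1.5 taken exactly. Totals of 131 to 134 fall below it even after rounding to one decimal.

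**Step 4, see whether another denominator was used.** 130/1.5 = 86.7 and 131/1.5 = 87.3. The article mentions no set of about 87 UCs. With 92 UCs (46 per arm, an exact 1:1 split), 131/92 = 1.42, which is still 1.4.

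**Separate check, Study setting.**

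- 93 × 20,000 = 1,860,000, against about 4,000,000 stated
- 4,000,000/93 = 43,011 per UC, against about 20,000 stated
- ratio 4,000,000/1,860,000 = 2.15

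Neither population enters a calculation in the article. Sample size justifies the 90 patients by the precision of proportions (margins of 0.1 for one arm and 0.07 overall), and cites the incidence of first-episode psychosis only as the reason for including every UC.

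**The case against.** The best defence is that the total governs and is unambiguous. The three bands are all expressed as totals and adjoin exactly, so a result of 131 to 139 cannot be Amber. The per-UC figure is a parenthesis, softened by an approximation, and is not listed as a further condition in the way that follow-up completion and healer participation are. The number 140 appears nowhere. The criteria are also advisory: the article says that clear criteria are hard to set in this field, that estimates will be weighed alongside the targets, and that the steering committee will advise. All of this stands, and it keeps the point small.

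It does not remove the point. The hedge covers rounding, but 1.41 does not round to 1.5, and the phrase also says at least. A reader who meets a mean of 1.41 beside that wording has to work out which figure was meant.

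Two stronger readings are tempting, and the documents support neither.

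- **A reader might infer two rival thresholds, 131 and 140,** and compare the chances of passing each. That comparison measures harm only if someone applies 1.5 strictly as a second rule, which the structure of the bands does not ask for.
- **A reader might infer that the population mismatch decides whether Green can be reached at all,** by setting 130 against one year's new cases. Recruitment is not confined to those. Participant eligibility criteria admits a first episode with no antipsychotic treatment, or at most 6 weeks of it, and sets no limit on the duration of untreated psychosis. Background and rationale puts that duration at 125 weeks in low/middle-income countries (125/52 = 2.4 years), so people whose illness began before the recruitment year can be eligible. The argument also needs the share of the population aged 14 to 25, which the article does not give.

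**Conclusion.** The point holds as a minor error of arithmetic or wording inside a prespecified criterion. The gloss should be about 1.4 per UC; as printed it is roughly 6% too high. The results affected are totals of 131 to 139 (means 1.41 to 1.49), or 131 to 134 if the mean is rounded to one decimal. This rests on two things the article states: all 93 UCs form the denominator, and Green starts immediately above the Amber limit of 130. It does not touch the sample size or any analysis, and because the criteria only guide advice, the decision is unlikely to turn on it.

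The population figures in Study setting are a separate, smaller inconsistency. They differ by a factor of 2.15 and cannot both be right if the 93 UCs make up the whole district, as the text implies. No stated calculation depends on them, and they add no weight to the point about the Green criterion.

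**What to change.** Keep the Green total at more than 130 and change the parenthesis to about 1.4 patients per UC, or delete it. This preserves the join with the Amber band. Only if the authors meant 1.5 per UC as the rule should the bands move, to Green at 140 or more and Amber at 90 to 139.

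Separately, reconcile the district population, the number of UCs and the mean UC population in Study setting, or say which part of the district the 93 UCs cover.

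The cost is one figure in the progression criteria and one in the setting description, with no effect on conduct. The first should be settled before recruitment results are reviewed.
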